### Study design

A double-blinded randomised controlled trial of adult healthy human participants experimentally exposed to escalating doses of
*S. pneumoniae* in the nasopharynx. The intervention vaccine will be PCV-13 (Prevnar-13) and the control vaccine will be normal (0.9%) saline. We will closely monitor study participants to ensure safety and tolerability of study procedures. We will measure immune protective responses to
*S. pneumoniae* challenge using mucosal (nasal, throat and saliva) and blood samples. We will invite participants for re-challenge 12-months after vaccination to determine longer-term immunological responses.

This study is based on the foundation of our ethically approved feasibility study
^
7–
9
^ and will utilise standard operating procedures successfully validated in Malawi. The study follows a logical sequence and the detailed schedule of visits (12 scheduled visits - Visit A to Visit L) and procedures carried out at each visit are described in
Table 1.

The sequence of stages followed is:

1.    
**Screening and recruitment:** Potential participants will be screened to ensure health and safety (
*Extended data*
^
16
^) as detailed in the Methods section.

2.    
**Randomisation:** Participants will be allocated to vaccination with PCV-13 or normal saline vaccination in randomised blocks (1:1 randomisation PCV13 vs. normal saline, double-blinded).

3.    
**Post vaccination samples:** Samples will be taken to confirm nasal carriage status and measure immune response.

4.    
**Primary inoculation:** Participants will be inoculated with
*S. pneumoniae* serotype 6B to the inside of each naris. We will sequentially increase the inoculation dose in groups of patients (20,000, 80,000 and 160,000 colony forming units per naris). One hundred and forty participants will receive the 80,000 dose to facilitate direct comparisons with our completed UK study
^
6
^. Forty participants will receive the 20,000 dose and twenty participants will receive the 160,000 dose. Total participants = 200.

**5.**    
**Detection of pneumococcal carriage:** Nasal wash samples will be taken, according to a standardized protocol, at days 2, 7, and 14 days post inoculation. Classical microbiological culture will determine nasal colonisation with pneumococcal serotype 6B at each time point.

**6.**    
**Immunology response measurements:** Blood, mucosal and nasal cell samples will be taken to determine the immunological response to nasal challenge.

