### Participant recruitment

Advertisements inviting healthy participants to participate will be widely placed. Areas will include physical notice boards, table display, electronic notice boards, the intranet/internet of local universities and colleges (with permission), social media, the local press, television and radio. Staff from the MLW team will be permitted to participate providing they are study team members.

Interested persons will be asked to contact the research team by text for further information. Once potentially interested participants have contacted the research team, they will then be invited to meet a member of the research team (information dissemination – visit A,
Table 1). A research team member will explain the study at the meeting and the Participant Information Sheet will be provided. Participants will then consider if they wish to continue (see
Table 1).

At visit B, the informed consent process will be conducted by either a research nurse or research doctors (
*Extended data*
^
16
^) who are formally delegated by the Chief Investigator, trained in good clinical practice (GCP), consent and the trial protocol. Following consent, inclusion and exclusion criteria will be applied as below.

**
*Inclusion criteria*
**

•Adults aged 18–40 years - ages chosen to minimise the risk of pneumococcal infection•Fluent spoken and written Chichewa or English - to ensure a comprehensive understanding of the research project, their proposed involvement and communication with all members of the research team

**
*Exclusion criteria*
**

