### Randomisation

Participants will be individually randomized to either PCV-13 (Prevenar) or normal (0.9%) saline vaccination prior to primary inoculation. A random number generator will be used to generate the randomization sequence and randomization occurs using block randomization with random block sizes of 6, 8 and 10 to ensure balanced vaccine allocations. An independent statistician will run the randomisation code for study group allocations and allocations will be stored on a secure electronic portal at MLW. The research team will be blinded to the vaccination group. Procedure: The study pharmacist will be fully unblinded and prepare each PCV-13 or normal saline according to the randomisation code. Individual doses will be prepared to maintain research team and participant blinding. Individual doses will be identified only by a randomisation identification number and barcode. Participants will be randomised on an electronic tablet immediately after screening is completed and they are confirmed eligible. The tablet will hold the randomisation identification number and barcode details. Subsequently, the vaccine barcode will be electronically confirmed against the participant identification number using the electronic tablet prior to administration. Unblinding will occur once microbiological reporting is completed for the final participant at visit G (14 days after primary inoculation). Participants entering the second stage (visit H) of the study will therefore be unblinded.

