### Sample size justification

The primary endpoint is the occurrence of pneumococcal colonisation determined by the presence of pneumococcus in nasal wash samples at any time point post inoculation detected using classical microbiology. Secondary endpoints will include density and duration of pneumococcal carriage in nasal wash.

Based on the pneumococcal dose of 80,000 cfu/naris and using data from our feasibility study
^
7,
8
^ and Liverpool-based studies
^
6
^, we estimate that 60% of the control (normal saline) group will be colonised with pneumococci following inoculation and 36% of the PCV-13 group, this equates to a 40% reduction in colonisation. We observed a 78% reduction in the UK based study
^
6
^. However, as Malawian data demonstrates decreased efficacy for PCV-13 in carriage reduction
^
10
^, we have powered the study at approximately half of this effect size. Based on these parameters, we will randomise 67 participants per arm for 80% at a 5% significance level (see
Table 2). To correct for any potential drop out, we will randomise 70 participants to each arm (total 140 participants for primary outcome).

**Table 2. T2:** Power calculations for PCV13 study.

Number per group	Carriage rate control	Carriage rate PCV-13 vaccine	PCV-13 carriage rate reduction	Power
**67**	0.6	0.45	0.25	0.41
**67**	0.6	0.42	0.30	0.55
**67**	0.6	0.39	0.35	0.69
**67**	0.6	0.36	0.40	0.80
**67**	0.6	0.33	0.45	0.89
**67**	0.6	0.30	0.50	0.95

An additional 40 participants will be randomised (1:1, PCV13 vs. normal saline) at the 20,000 pneumococcal dose. A further 20 participants will be randomised (1:1, PCV13 vs. normal saline) at the 160,000 pneumococcal challenge dose. These doses will be used to explore the effects of differential pneumococcal exposure on PCV-13 vaccine efficacy. Recent methodological developments in vaccine efficacy estimation highlight important gains derived from the use of multiple-dose over single-dose experimental designs
^
25
^. By extending our core experiment with smaller groups of participants at doses below and above 80,000 CFU, we will be in a position to not only apply the new methods to a human system for the first time, but also test their performance against a previously established mathematical model
^
25

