### Social science analytical plan

The social science evaluation requires qualitative data to understand volunteer perspectives of benefits, challenges, tolerability of study procedures, and any potential unintended effects through the study. All participants will be asked to complete an exit questionnaire upon completion of visit G (and visit L if consented for the second phase of the study) (
*Extended data*
^
27
^). This questionnaire will be completed by the participant on a tablet computer. Any participant who expresses concern(s) or dissatisfaction will be offered the opportunity to discuss in more detail as part of a semi-structured exit interview conducted as a separate appointment.

In the event that there are several structured exit interviews, all data collected will be audio-recorded and transferred to a qualitative data analysis software package (NVIVO), to enable analysis. Data will be analysed following broad deductively defined themes and inductively derived sub-themes. We will employ a combination of thematic coding in NVivo and use of frameworks to compare perspectives between different stakeholders (participants and study team members). Two researchers will undertake initial coding of an initial small number of transcripts, and then discuss and agree themes for further coding in the event that there are any further transcripts. Analysis will be on-going during fieldwork, using an iterative approach to identify emerging themes that can be clarified or explored further through later data collection. Data will be triangulated between methods and participant groups to cross-check information and provide a more comprehensive analysis. At this point, given responses in the feasibility study, we consider it unlikely that there will be a significant volume of exit interview material to analyse.

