### Ethical considerations

**
*Autonomy.*
** The participants will be given high-quality information that is written and spoken using common lay terms without jargon to allow them to understand the research objectives and the risks and benefits of all procedures. They will then be given time to consider the information before consenting to any involvement. At no stage should the participant feel pressured or persuaded into participating in the research study.

Participants have the right to withdraw their consent and therefore withdraw from the study at any time without giving reason. If a participant withdraws from the study, we will recruit an alternative participant to complete the study.

**
*Non-maleficence.*
** Inoculation of
*S. pneumoniae* will be as per the established and safe protocols and will be performed by highly trained staff with close supervision (24hr on call access to medical professionals involved in the study) and follow-up. Specific inclusion and exclusion criteria are set to further protect the participant. Experience and trained research staff will perform venepuncture and nasal sampling.

**
*Beneficence.*
** Participants will receive a health check including HIV-infection status assessment when taking part in this study. Participants also have the potential to benefit from completed vaccine schedules during the study. Patients randomised to normal saline will be offered PCV-13 upon completion of study related activities at visit L. In addition, participants may benefit from a better understanding of clinical research, they may also benefit from a sense of contributing to medical research in a valuable way. Participants will be remunerated for their time and inconvenience – discussed below.

**
*Justice.*
** This must be balanced with non-maleficence. Inclusion and exclusion criteria are in place primarily to protect individuals from undue risk.

**
*Ethical approvals.*
** Ethical approvals for this study have been granted in country by the Malawi National Health Sciences Research Committee (NHSRC, REF: 16/07/2519) and from a Liverpool School of Tropical Medicine (LSTM) institutional perspective (REF: 20-021).

**
*Trial registry.*
** This trial is registered with the Pan African Clinical Trial Registry (PACTR, REF:
PACTR202008503507113).

**
*Regulatory approval.*
** The trial has been approved by the Malawi Pharmacy and Medicines Regulatory Authority (PMRA/CTRC/III/10062020121)

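### As worded, the staff rule admits MLW staff only if they belong to the study team; a 'not' was most likely dropped, and no eligibility criterion corrects it

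*Protocol article*

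**What the plan says.** Participant recruitment in the Protocol article sets out how volunteers will be found and then states the rule for institutional staff: "Staff from the MLW team will be permitted to participate providing they are study team members". The inclusion criteria that follow cover age and language. The exclusion criteria cover health, exposure, medication, smoking, other trials and carriage of serotype 6B. Neither list mentions staff.

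Other parts of the article bear on the rule:

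- Study design describes "A double-blinded randomised controlled trial of adult healthy human participants experimentally exposed to escalating doses of" the challenge organism.
- Randomisation says "The research team will be blinded to the vaccination group", with one stated exception: "The study pharmacist will be fully unblinded and prepare each PCV-13 or normal saline according to the randomisation code".
- Study endpoints and Determination of colonisation base the primary outcome on classical culture of nasal washes at days 2, 7 and 14. Colonies are identified by appearance, haemolysis, optochin and bile tests and latex agglutination. Study setting places the laboratory work at MLW.
- The Social science analytical plan will use frameworks to "compare perspectives between different stakeholders (participants and study team members").
- Study status reports 40 participants screened and randomised by submission on 20 August 2021, with the study paused since 16 June 2021.

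**The concern.** An eligibility rule is applied at recruitment, so its literal wording matters more than that of a background sentence. This one selects the staff whom a blinded challenge trial would ordinarily keep out and turns away MLW staff with no role in the study.

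Two features of the trial are exposed. The first is allocation concealment from the participant: a person who prepares doses from the code cannot also be a blinded recipient. The second is independence of outcome assessment: the primary endpoint comes from samples that the team collects and cultures, and the article contains no rule keeping a team member away from their own sample.

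**Working it through.** No figure in the plan rests on this sentence, so the check is textual.

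**Step 1. Literal meaning.** 'Providing' introduces a necessary condition. With S for MLW staff and T for study team membership, the sentence says that a person in S may take part only if also in T.

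| Person | Rule as printed | Rule with 'not' inserted |
|---|---|---|
| MLW staff, on the study team | admitted | barred |
| MLW staff, not on the study team | barred | admitted |
| Not MLW staff | not addressed | not addressed |

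**Step 2. Is it corrected elsewhere?** The listed criteria contain no staff item. The closest is the item leaving uncertain cases to the principal investigator, which is a general discretion and does not address staff. The sections on randomisation, safety and ethics do not restate or amend the rule. It is current text, outside any amendment log, and the sentence is complete.

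**Step 3. Set the printed rule beside the rest of the article.**

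- *Unblinded pharmacist (Randomisation).* Doses carry a randomisation number and barcode, and the pharmacist prepares them from the code. A pharmacist who enrolled could link their own number to PCV-13 or saline. This is a direct conflict with a double-blind design.
- *Blinded research team (Randomisation).* An independent statistician runs the code, allocations sit on a secure portal, and unblinding waits until microbiology is reported for the last participant's visit G. A blinded nurse or microbiologist who enrolled would not learn their allocation through these procedures. There is no direct conflict here.
- *Culture endpoint (Determination of colonisation).* Staff who take washes or read plates could be participants, and nothing stated stops them handling their own samples. This is a gap in protection, not evidence that it would happen.
- *Two groups (Social science analytical plan).* Participants and study team members are compared as different stakeholders. The printed rule lets one person be both, so the fit is poor.

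**Step 4. Which wording was meant?** A proviso admitting only the trial's own team serves no evident purpose and sits badly with the points above. The same sentence with 'not' is an ordinary safeguard. A dropped word is therefore the most likely explanation, though the article does not say so.

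**Step 5. Sample size.** For 60% against 36%, with a two-sided 5% level (sidedness is assumed, as the article does not state it), pooled variance and no continuity correction, the normal-approximation formula gives 67 per arm. Power at 67 is 0.411, 0.550, 0.685, 0.801, 0.889 and 0.946 across the six rows of Table 2, against the printed 0.41, 0.55, 0.69, 0.80, 0.89 and 0.95. The plan's figures reproduce, and the staff rule enters none of them.

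**Step 6. How much recruitment is affected?** The target is 200 inoculated. With 40 randomised at submission, at least 200 − 40 = 160 were still to be randomised under whatever rule applies.

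**The case against.** The strongest reply is that this is a misprint in a journal article, that the full protocol and participant information are not shown, and that the working documents may carry the right wording. That is a fair limit: confidence attaches to the printed sentence, not to what recruiters were told. It does not remove the point, because the article states the rule and states it wrongly.

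Several stronger readings are tempting and are not supported.

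- *That the rule breaks blinding for any team member.* It does so directly only for the pharmacist. For the others, the procedures under Randomisation still hold.
- *That it contradicts the voluntariness statement.* Ethical considerations says "At no stage should the participant feel pressured or persuaded into participating in the research study". Permission to take part is not pressure, so the two sentences can both stand. Concern about an employer's influence would in any case apply to all MLW staff, including those the amended sentence would admit.
- *That the bias can be sized from the 70 randomised per arm at the main dose.* One participant in 70 is the weight of any single outcome. It says nothing about how often this rule would cause an error.
- *That team members have been enrolled, or that the investigators intended it.* The article shows neither.
- *That line managers should be excluded too.* Nothing in the article calls for this.

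It can also be said that a log check matters little for the primary comparison. Dose escalation starts with 40 participants at 20,000 CFU, so the 40 already randomised are apparently that exploratory group and not the 140 in the primary analysis. That stands as an inference, and it lowers the stakes of the look-back. It does not affect the need to settle the rule before the main group is recruited. PCR confirmation of the cultured washes is a partial safeguard, but the primary endpoint remains the culture result.

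**Conclusion.** The point holds as an error in an operative recruitment rule. As printed, it admits the trial's own team, bars other MLW staff, and is not corrected anywhere in the article. It conflicts directly with blinding for the study pharmacist, leaves staff who collect or culture samples free to be participants, and fits poorly with the separation of participants and team in the social science plan.

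The effect on the result cannot be estimated from the article and may be nil; sample size and power are untouched. The conclusion assumes that 'providing' has its ordinary meaning and that the study pharmacist and the staff handling samples are MLW employees who count as study team members, a term the article does not define. That a 'not' was dropped is inference. If the wording was intended, the article gives no safeguard to go with it, and it would still need to be justified.

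**What to change.** 1. Compare the sentence with the approved full protocol and the screening forms in use.
2. Correct it so that MLW staff may take part providing they are *not* study team members.
3. List study team membership as an exclusion criterion, so that the rule is applied at screening and does not rest on a sentence about advertising.
4. Check the enrolment log of everyone already randomised (40 at submission) for study team members, and report what is found.

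The cost is one word, one line in the criteria and a short review of the log. If the full protocol already has the right wording, a correction to the article is enough for the text. No analysis or sample-size change follows.

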### Screening and preliminary assessment

Following consent, inclusion and exclusion criteria, data and samples will be collected.

•     
**Initial clinical examination** will include a focused clinical history and targeted clinical examination involving auscultation of the lung fields and heart sounds. Participants will be informed if their clinical examination is normal. Should a previously unrecognised abnormality be identified, this will be explained to the individual, and appropriate investigations and follow-up will then be arranged by the study team. Further participation will be determined at the discretion of the study doctor dependent on the nature of the abnormality detected. If the participant is not eligible due to an acute illness, they may be re-screened at a later date with their verbal consent.

•     
**Blood samples** will be obtained using venepuncture by an appropriately trained team member. A maximum of 100mL of blood will be collected in each phase of the study (total 200mL if participant consents to re-challenge after one year) for analysis including a full blood count. The volume of blood collected for each laboratory test is detailed in
Table 1. Participants with an abnormal full blood count will be excluded from the study as determined by the clinical team.

•     
**Nasosorption** will be obtained before the nasal wash. The strips are similar to blotting paper and developed by Hunts Development Ltd (UK). Strips collect concentrated nasal lining fluid before the nasal wash to measure inflammatory responses induced by infection that may be associated with increased colonisation density and acquisition. Concentrated nasal fluid will be used to measure cytokine levels by multiplex bead array. Blotting paper will be held inside the nostril for up to 3 minutes until soaked. These will then be removed and placed in a microcentrifuge tube for storage.

•     
**Nasal wash** will be performed using an established method
^
18
^. This is a well-used and validated technique to collect nasal bacterial specimens used successfully during our feasibility study. Briefly, 5ml of sterile saline is instilled and held for a few seconds in the nares before being expelled into a sterile Galli pot. This is repeated twice in each naris using 20ml saline in total. In the event of nasal wash loss (defined as cough/sneeze/swallow), the procedure may then be repeated to obtain an adequate specimen. Should the nasal wash reveal natural colonisation of pneumococcus, the participant will continue in the study and receive the inoculation as per protocol, unless the natural serotype is identified as 6B, in which case the participant will be excluded from the study prior to inoculation (primary outcome cannot be determined). All pneumococcal carriage negative participants will continue in the study.

•     
**Nasal cells** will be collected using a nano-sampling method in which cells are obtained through minimally invasive superficial nasal scrape biopsies (Rhino-Pro Nasal Curette, Morphew Curettes). Experience from our feasibility study
^
7
^ demonstrates that participants can be biopsied multiple times with no significant side effects. Nasal cell samples will be obtained after nasal wash samples have been taken. Up to 4 samples (2 per nostril) will be obtained at each nasal sampling visit. If the researcher finds that the sample is insufficient, for example no cells are visible on the rhinoprobe, the sample can be repeated immediately. The rhinoprobes are placed in transport media immediately after collection.

•     
**Throat swabs** will be performed by simple posterior pharyngeal swabbing on a dry swab and placed into culture media. This test will be used to determine infection with SARS-CoV-2 by viral PCR prior to inoculation as part of screening and stored for batch classical microbiological testing (data not used for screening).

•     
**Saliva** will be collected by a salivette held for saturation or a spit in the tube.

•     
**Urine sample** will be taken for a pregnancy test as part of the safety screening. 

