**7.**    
**Re-screen and recruitment**: Participants will be invited to be re-challenged with pneumococcus. We will re-screen to ensure health and safety as detailed in Methods.

**8.**    
**Final inoculation:** Participants will be inoculated with
*S. pneumoniae* serotype 6B to the inside of each naris (as per stage four). We will use a single dose of 80,000 cfu/naris. This is the most established dose based on completed UK studies with robust colonisation data.

**9.**    
**Detection of pneumococcal carriage:** Nasal wash samples will be taken, according to a standardized protocol, at days 2, 7, and 14 days post inoculation (as per stage five). Classical microbiological culture will determine nasal colonisation with pneumococcal serotype 6B at each time point.

**Table 1. T1:** Study procedures and sampling schedule. Study visit A may occur for up to one month before study visit B. There will be a flexibility of up to 10 weeks after study visit B (1–11 weeks) to allow for staggering to inoculate a safe number of participants per week. Thereafter, the schedule will fix as per the table (e.g. if study visit D occurs at week 9, then E will be at 9, F at 10 and so on). There will be a further flexibility ± two weeks at visit H to facilitate appointment booking. There will be a tolerance of ± two working days for study visits F, G, K and L. FBC: full blood count; PBMCs: peripheral blood mononuclear cells; RNA: ribonucleic acid. *This is for immune measures (transcriptomics) and is not a genetic test. Serum will be used for serological testing; inflammatory markers; and biochemistry. Pregnancy test for female participants only.

Study Visit	A	B	C	D	E	F	G	First phase of study completed. Participants invited for second phase consent one -year post vaccination	H	I	J	K	L
Study Week		1	5	6	6	7	8		53	54	54	55	56
Day post inoculation				0	2	7	14			0	2	7	14
Consent (Written)		x							x				
Consent (Verbal)	x	x	x	x	x	x	x		x	x	x	x	x
Clinical Exam		x							x				
Vital Signs		x	x	x	x	x	x		x	x	x	x	x
Medical History		x							x				
Screen for AEs		x	x	x	x	x	x		x	x	x	x	x
Randomisation		x											
Vaccination		x											x
Inoculation				x						x			
HIV test		x	x						x				
Pregnancy test		x	x						x				
FBC (2.5ml)		x							x				
PBMCs (18ml)		x	x		x	x	x		x		x	x	x
Serum (2.5ml)		x	x		x	x	x		x		x	x	x
Blood RNA (2.5ml) *		x	x		x				x		x		
Nasosorption		x	x	x	x	x	x		x	x	x	x	x
Nasal Wash		x	x		x	x	x		x		x	x	x
Nasal cells		x	x		x	x	x		x		x	x	x

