### Remuneration

It is intended that financial factors will not significantly influence an individual's decision to participate in this study. We reimburse participants for out-of-pocket expenses such as travel, and compensate time spent and burden. The sums offered in this study are consistent with remuneration guidelines published in Malawi, paid pro-rata (per activity and not dependent on study completion)
^
35
^.

If a participant withdraws from the study early, they will be compensated for the parts they took part in up until the time they withdrew. Payments are summarised in
Table 3 and
Table 4, MK 11,000 will be paid at the end of each study visit for Phase 1. If the volunteer consents to participate in Phase 2, MK 10,000 will be paid at the end of each study visit. For volunteers who are approached and agree to be interviewed for social science activities at the end of visit G and visit L there will be an additional MK 7000 offered to compensate for their time and transportation.

**Table 3. T3:** Research participant remuneration for Phase 1 (visits A-G). *Accommodation and board costs will be paid directly by the research team. Participants will not receive compensation to attend the information visit (vist A). Visit D will cause mild discomfort. Visits B, C, E, F and G will cause mild/moderate discomfort.

MARVELS Research Participant Remuneration (based on Malawian guidelines ^ 35 ^)			
Reimburse expenses	Rate in MK	Number of events	Total
a) Transport	900	7	6,300
b) Subsistence (one meal)	1500	7	10,500
c) Accommodation (one night) *	15000	3	0

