**Compensation**			
Total time travelling (hrs)		7	
Total time in research facility (hrs)		21 research 72 accommodation	
Time in days (day = 8 hours)	1000	12.5	12,500
Procedure A (mild discomfort)	2000	1	2,000
Procedure B (moderate discomfort)	6000	5	30,000
Procedure C (long or complex)	10000		
**TOTAL for study** **(Phase 1)**			65,800
**AVERAGE per visit**			11,000

**Table 4. T4:** Research participant remuneration for Phase 2 (visits H-L). *Accommodation and board costs will be paid directly by the research team. Visit I will cause mild discomfort. Visits H, J, K, and L will cause mild/moderate discomfort.

MARVELS Research Participant Remuneration (based on Malawian guidelines ^ 35 ^)			
Reimburse expenses	Rate in MK	Number of events	Total
a) Transport	900	5	4,500
b) Subsistence (one meal)	1500	5	7,500
c) Accommodation (one night) *	15000	3	0

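### The phase 1 blood draws in Table 1 add up to 112.5 mL, above the stated maximum of 100 mL per phase

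*Protocol article*

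**What the plan says.** The Blood samples item under Screening and preliminary assessment sets the limit: "A maximum of 100mL of blood will be collected in each phase of the study". It then gives the overall figure: "total 200mL if participant consents to re-challenge after one year". The next sentence names the source of the component volumes: "The volume of blood collected for each laboratory test is detailed in" Table 1.

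Table 1, in the Study design section, has four blood rows, each with a volume and a mark at each visit where the sample is taken: full blood count (FBC) 2.5 mL, PBMCs 18 mL, serum 2.5 mL, and "Blood RNA (2.5ml"). The titles of the remuneration tables confirm which visits belong to which phase: A to G are phase 1 and H to L are phase 2.

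**The concern.** The article gives both a ceiling and the itemised volumes that should sit under it, and links the two. If the items exceed the ceiling, both statements cannot be followed. Staff who draw what Table 1 schedules exceed the stated maximum. Staff who keep to the maximum cannot take every scheduled sample in full.

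Two things are at stake. One is the accuracy of a figure on how much blood is taken from healthy volunteers, in a study with a phase 1 target of 200 participants. The other is the completeness of the late phase 1 blood samples. Cellular responses in peripheral blood are among the secondary immunology measures, and the Analysis plan intends longitudinal comparisons of immunological parameters.

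**Working it through.** **Inputs.** Volumes and marked visits come from Table 1. The limits, 100 mL per phase and 200 mL in total, come from the Blood samples item.

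**The plan's own figures.** The total is consistent with the per-phase limit: 2 × 100 = 200 mL. The question is whether the schedule fits under it.

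**Formula.** Volume per phase = sum over the four blood rows of (mL per draw × number of marked visits).

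| Sample | mL per draw | Phase 1 visits | Phase 1 mL | Phase 2 visits | Phase 2 mL |
|---|---|---|---|---|---|
| FBC | 2.5 | B | 1 × 2.5 = 2.5 | H | 1 × 2.5 = 2.5 |
| PBMCs | 18 | B, C, E, F, G | 5 × 18 = 90 | H, J, K, L | 4 × 18 = 72 |
| Serum | 2.5 | B, C, E, F, G | 5 × 2.5 = 12.5 | H, J, K, L | 4 × 2.5 = 10 |
| RNA | 2.5 | B, C, E | 3 × 2.5 = 7.5 | H, J | 2 × 2.5 = 5 |
| **Sum** | | | **112.5** | | **89.5** |

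- Phase 1: 112.5 − 100 = 12.5 mL over (12.5%).
- Phase 2: 100 − 89.5 = 10.5 mL under.
- Both phases: 112.5 + 89.5 = 202 mL, which is 2 mL (1%) over 200 mL.

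The two phases differ by 23 mL. That is exactly the visit C draw (18 + 2.5 + 2.5), which has no counterpart in phase 2.

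**Where phase 1 passes the limit.**

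| Visit | Drawn at visit (mL) | Cumulative (mL) |
|---|---|---|
| B | 2.5 + 18 + 2.5 + 2.5 = 25.5 | 25.5 |
| C | 18 + 2.5 + 2.5 = 23 | 48.5 |
| E (day 2) | 18 + 2.5 + 2.5 = 23 | 71.5 |
| F (day 7) | 18 + 2.5 = 20.5 | 92.0 |
| G (day 14) | 18 + 2.5 = 20.5 | 112.5 |

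After visit F, 100 − 92 = 8 mL remains against 20.5 mL scheduled at G. Serum takes 2.5 mL and leaves 5.5 mL for an 18 mL PBMC draw, a shortfall of 12.5 mL.

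**Other ways of counting phase 1.**

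- Without FBC: 112.5 − 2.5 = 110 mL.
- Without FBC and RNA: 112.5 − 10 = 102.5 mL, still over.
- PBMCs alone: 90 mL, which meets the limit only by ignoring the other three rows.
- Without any visit B blood: 112.5 − 25.5 = 87 mL. The text does not support this. The Blood samples item includes the full blood count in the blood it limits, and the only phase 1 FBC is at visit B.

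**Is the table misread?** The PBMC and serum marks fall at the same visits as the nasal wash marks. Those after inoculation agree with the day 2, 7 and 14 nasal washes described in Study design. The rows show no sign of extraction damage.

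**The case against.** The arithmetic is not open to much dispute. The article nowhere says that tubes are shared, that volumes are reduced, or that screening blood is exempt. Nor is this a detail left to a fuller protocol, because both the limit and the volumes are printed here. The fair objections concern the consequences, and several stronger readings a reader might infer do not stand.

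- **Every phase 1 participant exceeds the maximum.** Not so. The total passes 100 mL only at visit G. Anyone excluded for serotype 6B carriage found at visit C, taken out of further visits for COVID-19, or withdrawn before G has at most 92 mL scheduled. The 202 mL applies only to those who also complete the optional second phase.
- **Day 14 serum is lost.** The 8 mL left at G covers the 2.5 mL serum sample. Only the PBMC draw is constrained.
- **Systematic missing data follow.** This holds only if staff enforce the maximum and sample earlier visits in full. The article says neither. The 12.5 mL could equally be spread over five PBMC draws at 12.5 / 5 = 2.5 mL each. The schedule is the same in both arms and the research team is blinded during phase 1, so nothing points to bias between arms.
- **The main result is at risk.** It is not. The primary endpoint, carriage density and carriage duration come from nasal wash. The paired immunological comparison in Sample size justification uses visits B and C, when cumulative blood is 48.5 mL.
- **A safety limit is broken.** The article states a maximum without giving a safety reason and does not list it among its safety measures. Nothing in it shows harm from a further 12.5 mL.

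These points narrow the consequences. They leave the mismatch itself untouched.

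**Conclusion.** The point holds as an internal contradiction. The schedule that the limit cites exceeds the limit in phase 1 by 12.5 mL (112.5 against 100 mL) for any participant sampled in full through visit G. Phase 2 complies on its own. The overall excess of 2 mL adds little, so phase 1 carries the finding.

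The effect on data is conditional: if the maximum is kept and visits B to F are sampled in full, the full day 14 PBMC draw cannot be taken. It is confined to secondary immunology.

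The conclusion assumes that each Table 1 volume applies to each marked visit, which is how the Blood samples item describes the table. The full protocol and the participant leaflets are not at hand, so whether they repeat the 100 mL figure is unknown.

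**What to change.** Reconcile the Blood samples item under Screening and preliminary assessment with Table 1, so that the stated maximum and the sum of scheduled volumes agree in each phase and overall. Check that the phase 1 and phase 2 participant information leaflets and consent forms, listed under Extended data, give the same figure. Whether the maximum or the schedule changes is for the investigators, sponsor and ethics committee to decide.

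The cost is a minor amendment to one sentence or to Table 1, plus the leaflets if they carry the figure. Study status says that protocol amendments need ethics committee and sponsor approval. At manuscript submission, 40 participants had been randomised and the study was paused, so most of the planned 200 were still to come.
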